## Abstract

**Background:**

Painful infectious mouth conditions are a common presentation to emergency departments. Although self limiting, painful ulcerative lesions and inflamed mucosa can decrease oral intake and can lead to dehydration. Oral analgesia is of limited efficacy and is often refused by the patient. Despite widespread use of oral 2% viscous lidocaine for many years, there is little evidence for its efficacy as an analgesic and in aiding oral intake in children with painful infectious mouth conditions. This study aims to establish the effectiveness of 2% viscous lidocaine in increasing oral intake in these children by comparing it with placebo.

**Methods/Design:**

This study is a randomised double-blind placebo controlled trial of children between 6 months and 8 years of age with painful infectious mouth conditions defined as gingivostomatitis (herpetic or non herpetic), ulcerative pharyngitis, herpangina and hand foot and mouth disease as assessed by the treating clinician in association with a history of poor oral fluid intake. It will be conducted at a single tertiary paediatric emergency department in Melbourne Australia.

20 patients have already been randomised to receive 2% lidocaine or placebo in a pilot study to determine the sample size in a preplanned adaptive design. A further 80 patients will be randomised to receive either 2% lidocaine or placebo. The placebo agent is identical to lidocaine in terms of appearance, flavour and smell. All clinical and research staff involved, patients and their parents will be blinded to treatment allocation.

The primary endpoint is the amount of fluid ingested by each child, expressed in ml/kg, within 60 minutes from the time of administration of the study mixture. Secondary endpoints are the proportion of patients ingesting 5 ml/kg and 10 ml/kg at 30 and 60 minutes after drug administration and the incidence of adverse events. Longer term outcomes will include the proportion of patients requiring hospital admission and length of emergency department stay.

**Discussion:**

This trial will define the role of 2% lidocaine in the treatment of painful infectious mouth conditions

**Trial registration:**

The trial is registered with the Australian and New Zealand Clinical Trials Registry - ACTRN12609000566235.

## Background

Painful infectious mouth conditions are a common presentation to paediatric emergency departments. These are usually viral conditions such as gingivostomatitis (herpetic and non herpetic), ulcerative pharyngitis, herpangina and hand foot and mouth disease. Most of the paediatric literature concerns primary herpetic gingivostomatitis (PHGS) caused by infection with the herpes simplex virus. Although self limiting, there is considerable morbidity from decreased oral intake. Amir et al found that 89% of patients with PHGS drank less than normal [1]. The oral lesions can persist for 7 to 18 days with the risk of dehydration [2]. The presence of extra-oral lesions in addition to intra-oral lesions is highly indicative of PHGS [3], and may be used to differentiate PHGS from other ulcerative mouth conditions of children: mainly herpangina and hand foot and mouth disease (both caused by the coxsackie virus). In herpangina, lesions are typically seen on the posterior portion of the oral cavity and palate, with an absence of extra-oral lesions. Hand foot and mouth disease typically has both intra-oral and extra-oral lesions and the distribution of characteristic lesions on the hands and feet distinguishes it from PHGS [4]. These findings are particularly valuable as the majority of PHGS cases are diagnosed on clinical findings alone. Treatment for such conditions is generally symptomatic and therefore a precise diagnosis is not critical as such.

The mainstay of care for children with gingivostomatitis is supportive and expectant. The primary goal of therapy in acute care is directed towards pain relief from ulcerative lesions and inflamed mucosa, thus facilitating oral fluid intake to prevent dehydration. Often, routine oral analgesia is the first mode of therapy attempted by parents at home. However, it may have little effect in the relief of pain and is often refused by the patient. If oral intake cannot be improved, there is a subsequent risk of admission to hospital for intravenous (IV) or nasogastric (NG) fluids. Amir et al [3] found that 3 out of 36 (8%) children presenting with herpes gingivostomatitis experienced dehydration and required hospitalisation for IV rehydration.

Treatment trials for painful infectious mouth conditions have focussed on the efficacy of acyclovir and similar antiviral agents for treating PHGS with controversy about the strength and weakness of the evidence of its efficacy [2,5,6]. Regardless, acyclovir use is of limited relevance where acute fluid intake of a child in the ED is concerned and the exact diagnosis is often not known. Many agents have been described for painful ulcerative mouth conditions in adults and children including gingivostomatitis, oral candidiasis and aphthous ulcers. Agents used for one or a number of conditions include viscous lidocaine, benzocaine preparations, diphenhydramine elixir, coating agents including Maalox, milk of magnesia and Kaopectate, antibiotics particularly chlorhexidine and tetracycline and topical steroids [7-21]. In a retrospective chart review of 48 non immune suppressed paediatric patients presenting with PHGS at the Children's Hospital in Buffalo, United States[2], all were treated with analgesics such as acetaminophen or ibuprofen, 35 were treated with a mixture of Maalox and diphenhydramine, 8 with acyclovir, 7 with viscous lidocaine and 11 received two or more of these therapies. A major textbook of Paediatric Emergency Medicine [10] mentions rinsing with viscous lidocaine, as well as "magic mouthwash" (a mixture of Kaopectate and Benadryl) as treatment options. 2% viscous lidocaine has been recommended in the study hospital ED Clinical Practice Guidelines (CPG) for the treatment of herpes gingivostomatitis for many years [9]. To date, however, there have been no RCTs investigating any topical anaesthetic for painful ulcerative conditions of the mouth in previously health children.

There are some data from adult ulcerative mouth conditions and patients with cancer related mucositis. In a double blind RCT Saxen et al [11] randomised 60 adults with aphthous ulcers to one of 3 treatment groups - 3% diclofenac in 2.5% hyaluronan, 2.5% hyaluronan or 3% viscous lidocaine. For spontaneous and stimulated pain a significant reduction in pain was shown in all 3 groups (p < 0.01) with no demonstrable difference between the 3 topical agents. Akhionbare and Ojehanon [12] randomised 30 patients with aphthous ulcers to either 2% plain lidocaine or 2% lidocaine with adrenaline. 87% of patients experienced a complete relief of pain after application of either solution. Although different etiologically, oral mucositis often results in unrelenting pain causing an inability to eat and drink with subsequent risk of malnutrition and dehydration. In this respect it is similar to severe infectious mouth conditions. Yet, a review of the literature on the management of mucositis demonstrates a lack of consensus of scientific opinion on optimal treatment for relieving painful mucositis [22] and the use of a large variety of different topical agents including diphenhydramine, viscous lidocaine, magnesium hydroxide and aluminium hydroxide (Maalox), nystatin and corticosteroids has been described [23]. RCT data are limited and a Cochrane review [24] found that there was "no proven and satisfactory treatment available" for oral mucositis in the adult population. Similarly, a paediatric review [22] revealed a paucity of controlled trials in children, highlighting that current practice is governed more by clinical experience rather than scientific evidence.

Lidocaine, the first amide-type local anesthetic, is commonly used topically for a number of indications. A flavoured 2% solution of lidocaine hydrochloride (2% viscous lidocaine, trade name Xylocaine Viscous^® ^Astra Zeneca) is commercially available. Local anaesthesia is achieved within approximately 5 minutes and the duration of anaesthesia lasts between 20 and 30 minutes [25]. The recommended maximum dose of lignocaine is 3 mg/kg, 3 hourly, which equals 0.15 ml/kg of 2% viscous lidocaine. Adverse events from topical lidocaine administration are uncommon and have only been reported when used beyond the recommended doses [26,27].

Ulcerative lesions and inflamed mucosa due to viral infections in children are frequent reasons for presentations and can be associated with decreased oral intake and the risk of dehydration. Despite their widespread use, at this time there are no data to support the use of topical agents, in particular topical lidocaine for painful infectious mouth conditions in otherwise healthy children. We set out to assess if 2% viscous lidocaine can increase oral intake in these children by comparing it with placebo.

## Methods/Design

### Study Aims

The primary research question of this study is whether topical 2% viscous lidocaine is effective in improving the poor oral intake associated with painful infectious mouth conditions compared to placebo in children within 60 minutes of administration.

### Study Design and Setting

This study is a randomised double-blind placebo controlled trial. It will be conducted at a single tertiary paediatric emergency department (ED) in the Royal Children's Hospital (RCH), Melbourne, Australia.

### Ethical Considerations

The study has ethical approval at the study hospital. All parents/guardians are provided with both verbal and written information about the study and written informed consent is obtained prior to enrolment of their child into the trial.

### Subject Selection

Children satisfying the inclusion and exclusion criteria who present to the recruiting hospital ED during the study period are eligible for enrolment.

### Definition of Disease State

The eligible participants will be patients aged 6 months to 8 years, who present with gingivostomatitis (herpetic or non herpetic), ulcerative pharyngitis, herpangina and hand foot and mouth disease as assessed by the treating clinician, in associated with a history of poor oral fluid intake (as assessed by parent and defined as oral fluid intake of less than 10 ml/kg of fluid in the preceding 2 hours).

### Inclusion and Exclusion Criteria

Inclusion and exclusion criteria are presented in Table 1. Exclusion criteria include hypersensitivity to any of the contents of the study medication or similar drugs (other amide local anaesthetics), and patients with diseases (such as epilepsy impaired cardiac conduction, bradycardia, impaired hepatic function) that may be complicated by the study drugs.

**Table 1 T1:** Inclusion and exclusion criteria

**Inclusion criteria - all of:**
Diagnosed by the treating doctor with ulcerative pharyngitis, herpangina, hand foot and mouth disease, herpetic gingivostomatitis OR non-herpetic gingivostomatitis
Parental complaint of child's poor oral intake
Intake of less than 10 ml/kg of fluid within 2 hours preceding presentation to RCH ED

**Exclusion criteria - any of:**
Presence of more than 2 vomits within 24 hours preceding presentation to RCH ED
Presence of active painful dental disease (caries, dental abscess) or painful recent mouth trauma, mouth burn, or post-operative state (minimum of 5 days)
Systemic toxicity related to infection, as defined by the treating doctor
Severe dehydration requiring immediate therapy, as defined by the treating doctor
Known allergy to local anaesthetic, gelatine, methylcellulose, cherry flavouring, paracetamol or ibuprofen
Chronic renal or liver impairment
History of epilepsy or cardiac disease
Presence of acute porphyria
Presence of malignancy
Current use of anti-arrhythmic drugs, xylocaine, phenytoin, cimetidine or beta-blockers, warfarin, lithium, angiotensin converting enzyme (ACE) inhibitors, thiazide diuretics, frusemide, aspirin, salicylates, probenecid, anti-diabetic medications, zidovudine, cardiac glycosides or methotrexate
More than 1 dose of 2% viscous lignocaine or medications containing lignocaine as the active ingredient for this episode of illness
Pre-existing upper airway obstruction and/or swallowing difficulties
Analgesia taken within 1 hour preceding enrolment to study Non-English speaking parents/guardians

RCH ED Royal Children's Hospital emergency department

### Patient Randomisation

Patients who fulfil the eligibility criteria and whose parents provide informed consent will be randomised to either 2% viscous lidocaine or placebo.

The randomisation schedule will be computer generated using block randomisation by the Clinical Biostatistics and Epidemiology Unit (CEBU, Murdoch Children's Research Institute, Melbourne, Australia). Random block sizes will be used. The randomisation will not be stratified. Sequentially numbered bottles of either lidocaine or placebo will be arranged according to this schedule by a study pharmacist. Once a patient has been randomised they will be given the next available study number which will equate to an allocation of study drug dispensed in two bottles (labelled Bottle A and Bottle B).

At the time of randomisation patients will be given a dose of study solution from Bottle A which will contain the study drug according to their random allocation. Bottle B will contain the alternative mixture i.e. lidocaine if randomised to placebo and placebo if randomised to lidocaine. After 60 minutes the treating clinician may prescribe a dose from this second bottle if clinically warranted. This ensures that all participants in the study have access to the active treatment.

All study drugs will be packaged in blinded containers stored in a locked cupboard labelled only with the study details and the study number. Only the study pharmacist will be aware of the treatment allocation.

### Randomised treatments

#### Study drug: 2% viscous lidocaine mixture (Xylocaine Viscous^®^, Astra Zeneca)

This is a viscous mixture of 2% lidocaine hydrochloride, made up with methyl hydroxybenzoate, propyl hydroxybenzoate, sodium hydroxide, saccharin sodium, cherry extract (water, flavour, citric acid and amaranth), carmellose sodium and water for injections. The dose of 2% viscous lidocaine at the RCH conforms to the local Paediatric Pharmacopoeia at 0.15 ml/kg [28].

#### Placebo: contains methylcellulose and cherry flavouring

The placebo will be made up by the RCH Pharmacy from stock ingredients. The placebo will be identical to the study drug in terms of appearance, flavour and smell.

### For both groups

0.15 ml/kg of lidocaine/placebo will be administered once at the time of randomisation by the treating nurse via a measured syringe to the oral cavity of the participant ensuring coverage to inflamed mucosa and ulcerative lesions. If the participant is mature enough, he/she will be instructed to gargle and spit out the study drug/placebo. If the participant is not mature enough to follow these instructions, he/she may swallow or spit out the study drug/placebo. It will be recorded if the lidocaine/placebo is spat out within 1-2 seconds of administration. Further lidocaine/placebo will not be administered.

With the exception of the bottles of study drug, 2% viscous lidocaine may not be prescribed by the treating clinician during the 90 minute study period or for the preceding 90 minutes due to risk of lidocaine toxicity.

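### The lidocaine ban runs 90 minutes before and 90 minutes after the first study dose, so on each side it is shorter than the protocol's own 3-hourly dose limit

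*Protocol article*

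**What the plan says.** **The limit.** The Background states: "The recommended maximum dose of lignocaine is 3 mg/kg, 3 hourly, which equals 0.15 ml/kg of 2% viscous lidocaine". It adds: "Adverse events from topical lidocaine administration are uncommon and have only been reported when used beyond the recommended doses".

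**The study dose.** Under Randomised treatments and For both groups, each child receives 0.15 ml/kg of lidocaine or placebo. Patient Randomisation provides a Bottle B holding the opposite mixture, which the clinician may prescribe after 60 minutes. A child too young to gargle is handled as follows: "he/she may swallow or spit out the study drug/placebo".

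**The ban.** For both groups exempts the study bottles and then says "2% viscous lidocaine may not be prescribed by the treating clinician during the 90 minute study period or for the preceding 90 minutes". The reason follows in the same sentence: "or for the preceding 90 minutes due to risk of lidocaine toxicity". The study period ends 90 minutes after Bottle A.

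**Eligibility.** Three lines of Table 1 bear on earlier lidocaine:
- It excludes "More than 1 dose of 2% viscous lignocaine or medications containing lignocaine as the active ingredient for this episode of illness", which accepts one earlier dose and sets no time limit on it.
- It excludes "Current use of anti-arrhythmic drugs, xylocaine, phenytoin" and other drugs, without saying what counts as current.
- It excludes analgesia in the hour before enrolment, without saying whether topical lidocaine counts.

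**The concern.** The rule exists to prevent lidocaine toxicity, and the only dose limit in the document is 3 mg/kg per 3 hours. Because an active study dose takes up the whole allowance, any other lidocaine within 180 minutes of it, before or after, exceeds the limit. The rule protects only 90 minutes before Bottle A and 90 minutes after it. If active Bottle B is given at 60 minutes, only 30 minutes after that dose are protected.

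Participants may be 6 months old, and some will swallow the dose. The Background rests the drug's safety on staying within recommended doses. Bedside staff are blinded, so they cannot tell whether Bottle A adds 3 mg/kg or nothing. The written windows therefore have to provide the protection.

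Non-study lidocaine at this site is plausible: "2% viscous lidocaine has been recommended in the study hospital ED Clinical Practice Guidelines (CPG) for the treatment of herpes gingivostomatitis for many years". Herpetic gingivostomatitis is one of the qualifying diagnoses.

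**Working it through.** **Inputs.** Limit of 3 mg/kg per 3 hours, i.e. 180 minutes (Background). Study dose of 0.15 ml/kg (For both groups). Ban from -90 to +90 minutes, with Bottle A at time 0 (For both groups). Bottle B from +60 minutes (Patient Randomisation).

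**Reproducing the stated dose.** 2% is 20 mg/ml, and 20 × 0.15 = 3 mg/kg. This matches the Background figure exactly, so one active bottle equals the full 3-hour maximum.

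**Length of the ban against the limit.** 90 / 180 = 0.5 on each side of Bottle A.

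**Time left uncovered.** Before the active dose, the limit looks back to (time of active dose − 180). After it, the limit runs to (time of active dose + 180).

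| Active dose | Side | Limit reaches | Ban reaches | Uncovered |
|---|---|---|---|---|
| Bottle A at 0 | before | 0 − 180 = −180 | −90 | 180 − 90 = 90 min |
| Bottle B at +60 | before | 60 − 180 = −120 | −90 | 120 − 90 = 30 min |
| Bottle B at +90 | before | 90 − 180 = −90 | −90 | 0 min |
| Bottle A at 0 | after | 0 + 180 = +180 | +90 | 180 − 90 = 90 min |
| Bottle B at +60 | after | 60 + 180 = +240 | +90 | 240 − 90 = 150 min |

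A dose at exactly −180 minutes meets the 3-hour interval and is not a breach.

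**Short intervals the rule allows.**
- A dose at −91 is 91 minutes before Bottle A, and 60 + 91 = 151 minutes before Bottle B at +60.
- Open lidocaine at +91 is 91 minutes after Bottle A, and 91 − 60 = 31 minutes after Bottle B at +60.
- All four intervals are below 180 minutes.

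**Dose administered.** With a non-study dose of d ml/kg, the total is 3 + 20d mg/kg. The article does not fix d. I assume half to full usual dose: d = 0.075 gives 3 + 1.5 = 4.5 mg/kg, and d = 0.15 gives 3 + 3 = 6 mg/kg. Any d above zero exceeds 3 mg/kg.

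**Check of the fix.** With 3 hours before dosing, an earlier dose is at least 180 minutes before Bottle A and at least 180 + 60 = 240 minutes before Bottle B at +60. With 3 hours after the last study dose, open lidocaine is at least 180 minutes after whichever bottle was active. Neither side breaches.

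**The case against.** The best defence is Table 1. The study drug is Xylocaine Viscous, so excluding current use of xylocaine excludes current use of the study drug. For a drug dosed 3-hourly, a child dosed 91 minutes ago could be called a current user. The one-dose line would then only cap past exposure. That reading is possible, but the term is undefined and the accepted earlier dose has no time attached, so the two lines together do not clearly exclude a single dose 91 minutes before. Nor does an enrolment criterion govern open lidocaine after +90 minutes.

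It may be said that a journal article leaves screening detail to the full protocol. That is fair for the meaning of current use. It does not excuse the stated 90-minute figure, which conflicts with the stated limit.

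It may also be said that 90 + 90 = 180. That spacing keeps an earlier and a later non-study dose 3 hours apart from each other. It does not keep either of them 3 hours from the study dose.

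Some of the case against does stand. A pre-dose breach needs an earlier dose in a limited window, enrolment despite Table 1, and an active bottle soon enough afterwards. The Limitations section is weak evidence of likelihood: it describes children given oral analgesia by mistake who then become ineligible, and does not mention lidocaine. The Background calls adverse events uncommon, and the article gives no toxicity threshold.

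A reader might infer more than the documents support:
- **That the protocol directs an excess dose, or gives two active study doses.** It does neither. Bottle B is always the opposite of Bottle A.
- **That 6 mg/kg is the expected exposure.** It is an upper bound for two full doses, and some of a dose may be spat out.
- **That the primary outcome is compromised.** The Background puts anaesthesia at 20 to 30 minutes, so on that figure a dose more than 90 minutes earlier should have worn off. Lidocaine after +90 minutes falls outside the 60-minute endpoint.

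**Conclusion.** The point holds as an internal inconsistency in a safety rule, on both sides of dosing. For Bottle A, 90 of the 180 minutes are unprotected before and 90 after. For active Bottle B at +60, 30 minutes are unprotected before and 150 after. A child treated within the rule could receive 4.5 to 6 mg/kg in under 3 hours, if the non-study dose is between half and the full usual amount, against a stated maximum of 3 mg/kg.

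This rests on reading the limit as 3 mg/kg in any 180 minutes, on administered rather than absorbed dose, and on Table 1 not reliably excluding a single recent dose. The number of children affected cannot be estimated from the article. The rule should be corrected because it concerns the safety of young children and the correction is cheap. It does not undermine the trial's comparison.

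**What to change.** Under For both groups, bar non-study lidocaine for 3 hours before dosing and for 3 hours after the last study dose, whether Bottle A or Bottle B. Counting from the last bottle lets staff apply the rule without unblinding.

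In Table 1, add an exclusion for lidocaine from any source within 3 hours before enrolment. The words on source matter because the present ban covers only prescribing by the treating clinician. The one-dose allowance can stay for doses older than 3 hours.

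The cost is two changed time windows and one added line in Table 1 and on the screening form. A few children would wait or become ineligible. At the pilot rate of 20 in 5 months, 20 / 5 = 4 per month, so each child lost costs about a quarter of a month of recruitment. Open lidocaine would also be delayed after the study: to +180 minutes if only Bottle A was given, or to 60 + 180 = +240 minutes if Bottle B was given at +60. Other oral analgesia remains available from 60 minutes under the existing procedure.
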